#### *YJJ – Administrative Records*

Research materials include electronic administrative health and justice system records from multiple sources listed below. Identifying information, including participant name, SSN, address, MRN, etc., will be used to link available data across systems for each YJJ sampled. The linkage process uses a combination of deterministic and probabilistic algorithms to identify records of the same individual across data sources. The ADAPT research team will then de-identify linked datasets for analysis. Participants will be linked to their data only via unique study ID generated by the research team. The linkage between subject identifying information and study ID will be permanently destroyed at completion of the study. Access to files containing identifiable subject information is limited to a list of investigators maintained in the project's approved IRB protocol.

- *Justice system involvement data:* We are able to capture all sample youth interactions within juvenile justice agencies from each county. Variables will include, but are not limited to, offense type, date of arrest/referrals, criminal history, length of detention stays or incarceration, case disposition requirements and recommendations, and urine drug screen results.
- *Health data:* We will collect any CMHC records (e.g., visit data, service referrals) available for all YJJ in intervention sites. We recognize that youth may receive services in locations other than the local CMHC. Thus, we will also collect administrative health data from the following sources:
  - CMHC records. We will access visit data through the LHS intervention. We will also gather initial screening data, including mental and substance use screening measures used by CMHCs. These measures will be self- or parent-report and vary based on CMHC protocols.
  - Medicaid insurance claims. We will access all behavioral health carve-out data across the entire 10-year data collection period, including services provided by the Medicaid Rehabilitation Option and health insurance coverage for youth in foster care. Medicaid claims data include all pharmacy, outpatient, emergency department, and inpatient encounters (which can be categorized by service type: mental health, substance use, physical health, reproductive health, trauma care, etc.). We will calculate visits based on ICD-10 codes, consistent with previous work.

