*Substance use care cascade.* A primary outcome of interest is the SU care cascade (Cascade). The Cascade includes a spectrum of outcomes. At any point in the Cascade, a young person can “drop out.” The earliest stage of the Cascade occurs within the juvenile justice system: identification of treatment need (i.e., screening and assessment) and referral to services. The latter end of the Cascade occurs within the CMHC: treatment initiation, engagement, and completion. We are interested in determining whether the LHS intervention is effective in improving the Cascade. We will evaluate this outcome utilizing administrative data on the entire population of YJJ across all 8 sites. We will gather Cascade data from the local CMHCs as well as Department of Child Services (DCS) and Medicaid. The reason for gathering data from DCS and Medicaid is they both provide funds for outpatient services. Thus, if a young person receives substance use services outside of the local CMHC, we will be able to gather at least a portion of it from these data sources. We may find that the effectiveness of LHS is improved for young people seeking services outside of the CMHC. With that said, we have collaborated with the largest CMHC of each jurisdiction and most jurisdictions only have one CMHC located in their county. We will also be able to control for time spent outside of the community by controlling for commitments to Department of Corrections (gathered from the juvenile justice data set) and residential placement (gathered from DCS and Medicaid).

*Criminal recidivism.* We will also assess whether the LHS intervention is effective in limiting recidivism. We will utilize the existing juvenile justice information system to assess recidivism. We will focus on the prediction of new criminal charges rather than charges associated with previous criminal behavior (e.g., technical violation, probation violation and warrants).

*Opioid-related outcomes.* By linking with data collected through the Regenstrief Institute Addictions Data Commons, we will be able to assess a variety of outcomes. This includes hospital and Emergency Department visits for opioid use disorders (OUD) as well as emergency medical service runs due to opioid use. These data elements are now incorporated within the Addiction Data Commons.

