|---------|----------------------------|-----------------------------------------------------------------------------|-------------------------------------------------------------------------------------------------------------------------------------------------------------------------------------------------------------------------------------------------------------------------------|
|         |                            | admin sample;
42 months LHS
intervention
sample                    | the LHS intervention on the Cascade (i.e., substance use treatment need identification, referral to services, initiation of services, and engagement in services).                                                                                                            |
| Primary | Criminal
recidivism     | 10 years, total
admin sample;
42 months LHS
intervention
sample | We will evaluate criminal recidivism across the 10-year administrative data collection period. We will assess if Cascade improvement is associated with decreased criminal recidivism. We will also assess if there are intervention-specific effects on criminal recidivism. |
| Primary | Opioid-related
outcomes | 10 years, total
admin sample;
42 months LHS
intervention
sample | We will use administrative data to assess opioid-related outcomes. We will assess if Cascade improvement is associated with decreased opioid-related outcomes. We will also assess if there are intervention-specific effects on opioid-related outcomes.                     |

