#### *Aim 4 Comparative Effectiveness Analyses*

##### *Aim 4 Analyses*

We will use standard step wedge analytic methods (see citations in reference list for PASS report). We will use repeated measures Poisson models to compare control vs LHS intervention conditions on the response rate ratio for the SU cascade outcomes and the opioid related outcomes. The Poisson or zero-inflated Poisson regression models will be performed using SAS GENMOD to fit repeated measures generalized linear models (GLIM) with generalized estimating equations (GEE) to account for the fact that event data for youth will be measured repeatedly over time and to account for the correlation due to within-organization clustering. The outcome data will be entered into the model as event counts for every 6-month period of the 36 months of implementation (6 months of control condition for all clusters, then 30 months of intervention), reported separately for each arrest record. Multiple arrests for the same youth will be used in the model. In the power analysis (described below), we conservatively based the power calculations on the number of unique youth arrested. The actual analysis will use a random effect to incorporate data from youth who have multiple arrests.

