The amount of time (in days) exposed to the implementation for each adolescent arrestee will be accounted for in the rate ratio by defining the "offset" variable as the natural log of the number of days of exposure for every 6-month period of implementation. The primary denominator will be the number of arrested youth in the rolling intake cohort (e.g., % referred as a percentage of the number in the arrestee intake cohort). For some outcomes, another separate outcome will be derived and analyzed using a smaller denominator (e.g., % referred as a percentage of YJJ in need of treatment). The denominator for % in need (i.e., % screened positive) will be YJJ screened. The denominator for the % engaged will be the YJJ initiated. Because some youth will have multiple arrests, they could also have multiple screenings. In addition, for a single arrest and single screening, there could be multiple referral events over any 6-month period; for a single referral, there could be multiple treatment initiation events; and for a single treatment initiation, there could be multiple occurrences of an engaged event (i.e., 2+ behavioral health visits within 30 days after initiation) over any 6-month period. Therefore, the model will capture these multiple events as counts for every 6-month period.

Covariate-by-6-Month-Period interactions will be tested to determine whether the outcome response rates changed differently over time for different values of covariates.

In addition, youth-level covariates (demographics and health visit data) will also be included as predictors.

In the next step of the model, we will include organizational-level (i.e., county-by-system [JJ and CMHC]) survey predictors including staff characteristics (JPO age, sex, and race/ethnicity, time in current position, highest/type degree, number of previous positions, salary, caseload size, job (dis)satisfaction rating, turnover intentions, and burnout rating), implementation variables (readiness,

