However, we acknowledge some youth will be placed out of the home (DOC and residential placement). Additionally, some youth will migrate out of the community (which will be assessed by address data from state-wide databases; INPC, Medicaid, & DCS). Thus, we conservatively estimate that roughly 70% of 2,170 (i.e., 1,519) adolescent arrestees per year will be available in-home in the community from the 8 counties (4,557 total over 36 months of implementation which includes 30 months of intervention plus 6 prior months in which all cohorts experience the control condition under the baseline period). Based on an annual 30% recidivism rate, we estimate that 30% (1,367) of the projected 4,557 arrests for this trial will represent repeated arrests from the same youth, yielding an estimated 3,190 unique youth available in the administrative data over the 36 months of the primary outcome measurement period. We will actually collect and use administrative data for 5 years (not just 6 months) prior to the start of intervention; however, to be conservative, the step wedge power calculation assumed only 6 months of prior baseline administrative data (i.e., 36 months of primary administrative measurement). Additionally, although all data (including multiple arrests for the same youth) will be used in the model, to be conservative for the power analysis, we assumed that the maximum sample size available for the power calculations is the number of unique youth (3,190).

Our design has 8 counties (i.e., clusters). A projected maximum available sample size of 3,190 unique youth, over the 36-month primary evaluation period, yields: (1) 531 youth per 6-month time period, (2) an average of 398 maximum youth per cluster over 36 months (*M* in the Step Wedge Design), and (3) an average of 66 youth per cluster per 6-month time period (*m* in Step Wedge design).

We used the PASS software to calculate power for a test of two poisson rates (control condition event rate vs treatment condition event rate) in a cluster-randomized step wedge design. Our step wedge design is an "incomplete design" in which a different number of clusters (i.e., counties) start the intervention at each step. Given 8 clusters and practical considerations, we decided to initiate intervention for 3 clusters in cohort 1, then in the next step another 3 clusters in cohort 2, and then in the next step another 2 clusters in cohort 3.

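### Criminal history and offense type are collected but enter no stated Aim 4 model, which leaves the planned Cascade–recidivism association open to confounding

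*Protocol*

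**What the plan says.** Four parts of the protocol bear on this.

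- **Covariates.** Aim 4 Analyses states: "In addition, youth-level covariates (demographics and health visit data) will also be included as predictors". Inclusion of Women and Minorities also commits to demographic covariates. Assessing Outcomes, in its cascade paragraph, adds "controlling for commitments to Department of Corrections (gathered from the juvenile justice data set) and residential placement", to allow for time away from the community.
- **Model.** Aim 4 Analyses uses repeated-measures Poisson models to "compare control vs LHS intervention conditions on the response rate ratio for the SU cascade outcomes and the opioid related outcomes". Recidivism is not named there, nor in the later step that adds staff-survey predictors. On repeat arrestees it says: "The actual analysis will use a random effect to incorporate data from youth who have multiple arrests".
- **Recidivism.** Outcome Measures lists criminal recidivism as Primary and plans two analyses. One is an association: "We will assess if Cascade improvement is associated with decreased criminal recidivism". The other is a treatment comparison: "We will also assess if there are intervention-specific effects on criminal recidivism".
- **Data.** For the justice records, YJJ – Administrative Records says: "Variables will include, but are not limited to, offense type, date of arrest/referrals, criminal history, length of detention stays or incarceration". Aim 4 Power says: "We will actually collect and use administrative data for 5 years (not just 6 months) prior to the start of intervention".

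**The concern.** A youth's earlier arrests are the natural baseline value for later arrests, and the study extracts them. They appear in no stated adjustment set.

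The two recidivism analyses are affected differently. Whether a youth is referred to treatment and engages is not randomised. It plausibly depends on prior record and offense type through the court disposition, and both plausibly predict rearrest. An association adjusted only for demographics, health visits and time in placement could therefore show a benefit or a harm that reflects only who gets into treatment. In the LHS-versus-control comparison the timing of LHS is randomised by county, so what is at stake is precision and chance differences in case mix among eight counties.

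**Working it through.** **1. The plan's own power figure.** Inputs from Aim 4 Power: the design matrix (8 counties, 6 periods; 3, 3 and 2 counties crossing over), 50 youth per county-period, ICC 0.01, rates 1.00 and 1.25, two-sided alpha 0.05. The Hussey–Hughes variance is

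Var = I·s²(s² + T·t²) / [(IU − W)s² + (U² + ITU − TW − IV)t²].

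Here I = 8, T = 6, U = 33 treated cells, W = 237 (squared column totals summed) and V = 141 (squared row totals summed), so the denominator is 27s² + 123t². With Poisson variance at the mean rate 1.125, s² = 1.125/50 = 0.0225 and t² = 1.125 × 0.01/0.99 = 0.01136. This gives SE = 0.0902 and power = Φ(0.25/0.0902 − 1.96) = 0.791. The plan states 0.80, so the figure reproduces. The calculation contains no covariates, so adding some alters no stated number.

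**2. Confounding of the association.** For a binary prior record that multiplies the rearrest rate by g, with prevalence p1 in engaged and p0 in non-engaged youth, a true null appears as

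B = [1 + p1(g − 1)] / [1 + p0(g − 1)].

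The documents give none of these inputs. Assume 40% have a prior record and rearrest rates are 0.4 with and 0.2 without one (g = 2).

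- Prior-record youth engage more (30% vs 20%): p1 = 0.12/0.24 = 0.50, p0 = 0.28/0.76 = 0.368, B = 0.300/0.274 = 1.10.
- Prior-record youth engage less (20% vs 30%): p1 = 0.08/0.26 = 0.308, p0 = 0.32/0.74 = 0.432, B = 0.262/0.286 = 0.91.

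A wider grid (g from 1.5 to 3):

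| p1 vs p0 | g = 1.5 | g = 2 | g = 3 |
|---|---|---|---|
| 0.30 vs 0.30 | 1.00 | 1.00 | 1.00 |
| 0.25 vs 0.35 | 0.96 | 0.93 | 0.88 |
| 0.20 vs 0.40 | 0.92 | 0.86 | 0.78 |
| 0.40 vs 0.20 | 1.09 | 1.17 | 1.29 |

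**3. Precision in the randomised comparison.** Multiply the within-county variance by (1 − ρ²), where ρ is the assumed correlation of the covariate with the outcome. For recidivism, take half the protocol's 30% a year (0.15 per six months) and its 66 youth per county-period.

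| Setting | ρ = 0 | 0.3 | 0.4 | 0.5 |
|---|---|---|---|---|
| Plan's input: rate 1.00, ratio 1.25, 50 per cell | 0.791 | 0.826 | 0.853 | 0.888 |
| Rate 0.15, ratio 1.25, 66 per cell | 0.231 | 0.248 | 0.265 | 0.289 |
| Rate 0.15, ratio 1.5, 66 per cell | 0.642 | 0.681 | 0.714 | 0.760 |

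The second row is the relevant one at the plan's smallest ratio: a gain of 2 to 6 points.

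Even this is generous, because a covariate can explain overdispersion but not pure Poisson noise. With a gamma frailty of variance θ, ρ = θ√(μ1μ2)/√[(1 + θμ1)(1 + θμ2)]. A 12-month count has mean μ1 = 0.3, and the outcome has μ2 = 0.15. For θ = 1, 2 and 4, ρ is 0.17, 0.29 and 0.45. Putting the variance λ + θλ² into the formula in step 1, the gain at ratio 1.25 is about 0.5, 1.3 and 3 points. At ratio 1.5 it is about 1, 3.5 and 8 points.

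**4. Whether a recent-arrest count is a clean covariate.** In the design matrix all eight counties are under LHS from period 4 (intervention months 13 to 18). Aim 4 Analyses enters each arrest record separately, and Aim 4 Power takes 30% of arrests as repeats. A rolling 12-month count would increasingly contain arrests made under LHS, which are themselves recidivism events.

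**The case against.** A reader might infer that the protocol fixes recidivism to be analysed without its baseline value. The text does not go that far. The Aim 4 model names cascade and opioid-related outcomes only, and the covariate sentence says what is included, not that nothing else may be. The control for placement stands outside that sentence, so the list is not exhaustive. An analysis plan not shown here could supply the recidivism model, and its absence from a protocol would not by itself be a fault. This stands, and it limits the point. What remains is that the protocol commits to a recidivism association and names adjustment variables, but does not use the collected variables most closely tied to that outcome.

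A reader might also infer that the LHS-versus-control estimate is biased. It is not: omitting a baseline covariate does not bias a randomised contrast, and the precision gain is small.

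The random effect for repeat arrestees may absorb some stable differences in offending. It does not adjust for a measured factor that is correlated with cascade success.

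Finally, the protocol does not define cascade improvement at youth level. If a county-period measure is meant, the example in step 2 does not apply. The comparison would still not be a randomised one.

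**Conclusion.** The concern holds in a limited form. The Cascade–recidivism association is open to confounding by prior record and offense type, both collected and neither in a stated model. It is too strong to say that it is confounded. The apparent rate ratios of 0.91 and 1.10 under a true null, and the wider 0.78 to 1.29, rest wholly on assumed prevalences and rate ratios and on a youth-level contrast. With equal prevalence in both groups there is no distortion.

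For LHS versus control the cost is precision and protection against chance imbalance, not bias. At 0.15 rearrests per six months and a ratio of 1.25 the gain is probably a few power points. Larger gains, up to 10 points, come from the generic control rate of 1.00 with ρ = 0.5. The correlations are assumptions; the documents give none. The change is worth making because it is cheap and a Primary outcome is involved.

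**What to change.** In Aim 4 Analyses, state that criminal recidivism uses the Aim 4 model, and extend the covariate sentence in two parts.

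(a) For the Cascade–recidivism association, adjust for the number of arrests or referrals before the index arrest, over a fixed look-back so that every record has equal history, and for index offense type as recorded at that arrest.

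(b) For the LHS-versus-control recidivism model, adjust for prior record counted only from arrests before one common calendar date that precedes the first cohort's LHS start, using the five pre-study years, so that LHS cannot affect the covariate.

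Do not use a rolling 12-month count as the main covariate in (b), because it would adjust the randomised comparison for a post-treatment outcome.

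The cost is a few lines of text and two derived variables from records already being extracted, with no new data or participants. The downside of (b) is that a count fixed before the trial predicts less well in later periods, so the precision gained will be modest.

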## Statistical Design and Power

### *Aim 3 Implementation Outcomes Analyses*

The analyses will proceed in two steps.

*Step 1.* We will use standard step wedge analytic methods (see citations in reference list for PASS report below). We will use linear mixed models to analyze repeatedly measured implementation variables to determine whether implementation variables change over time from the control to intervention conditions. Organizational survey data will be collected at the county level (from 164 JJ staff) and from the health system level (from 231 CMHC staff) for a total of 395 surveys collected at six time points at 6-month intervals: Study Months 8, 14, 20, 26, 32, 38. The following continuous scale scores will be analyzed in a separate model as the dependent variable: perceived readiness to implement new innovations (ORIC), climate support of adopting new innovations (ICS), organization's leadership support of implementation of evidence-based practice (ILS), and collaboration alliance between JJ/CMHC (Effective Collaboration subscale). The models will contain random effects to account for the clustering of survey participants within county and health system organizational levels. The models will contain the following independent variables: Time (Month 8, 14, 20, 26, 32, 38), and survey covariates (JPO age, sex, and race/ethnicity, time in current position, highest/type degree, number of previous positions, salary, caseload size, job (dis)satisfaction rating, turnover intentions, and burnout rating). The Time effect will be tested to determine whether implementation outcomes change over time. The Covariate-by-Time interaction will be tested to determine whether the implementation outcomes changed differently over time for particular covariate values. Alternative time covariance structures (e.g., autoregressive) will be considered. Alternative models will be compared with Akaike Information Criterion (AIC), with lowest AIC indicating the better model statistically.

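### The Aim 4 effect model adjusts for health visits with no time limit, so outcome events and care after LHS start can enter as predictors and bias the LHS rate ratio

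*Protocol*

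**What the plan says.** In the Protocol, Aim 4 Analyses, a repeated-measures Poisson model compares the control and LHS conditions on the Cascade and opioid outcomes. Before the text moves on to a further modelling step with survey predictors, it adds that "youth-level covariates (demographics and health visit data) will also be included as predictors". No time window is attached to the visits.

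The same records supply several of the outcomes:

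- YJJ – Administrative Records, on health data: "We will collect any CMHC records (e.g., visit data, service referrals) available for all YJJ in intervention sites", and "Medicaid claims data include all pharmacy, outpatient, emergency department, and inpatient encounters".
- Assessing Outcomes, on the Cascade: "We will gather Cascade data from the local CMHCs as well as Department of Child Services (DCS) and Medicaid".
- Aim 4 Analyses define an engaged event as "2+ behavioral health visits within 30 days after initiation".
- Assessing Outcomes, on the opioid outcomes: "This includes hospital and Emergency Department visits for opioid use disorders (OUD) as well as emergency medical service runs due to opioid use".

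Assessing Outcomes also plans to allow for time away from the community by "controlling for commitments to Department of Corrections (gathered from the juvenile justice data set) and residential placement". It does not say how this enters the model.

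The later Aim 4 step adds staff characteristics, implementation scores and SIC fidelity scores, to see whether they predict the response rates. Separately, the Aim 3 Step 1 mixed model lists "job (dis)satisfaction rating, turnover intentions, and burnout rating" among its covariates, with surveys at six time points.

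**The concern.** A covariate in an effect model should not be something the intervention can change, and it should certainly not contain the outcome. LHS is meant to produce more treatment visits. If the visit covariate counts visits after arrest, part of the increase LHS produces sits on the right-hand side of the equation. The coefficient for LHS then answers a different question: whether outcome events differ between conditions among youth with the same number of visits. That is not the total effect of LHS.

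Placement raises the same issue. Commitment or residential placement can follow the arrest and the start of LHS. The protocol's own description of DCS data treats residential placement as a behavioral health service that DCS pays for. Conditioning on it may therefore condition on care that follows a referral.

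The Cascade and the opioid outcomes are both listed as primary in the Outcome Measures table, so the estimates at stake are the main effectiveness results. The overlap is clearest for initiation, engagement and opioid events. It is weaker for screening and need identification, which arise within the justice system.

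**Working it through.** **1. The plan's own power figure, as a reference point.** Inputs from Aim 4 Power: 8 clusters, 6 periods, cohorts of 3, 3 and 2 starting in periods 2, 3 and 4, m = 50 youth per cluster-period, ICC 0.01, two-sided alpha 0.05, rates 1.25 and 1.00. The Hussey-Hughes variance is

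Var = K·s·(s + T·τ²) / [(K·U − W)·s + (U² + K·T·U − T·W − K·V)·τ²].

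- From the design matrix: U = 33, W = 9 + 36 + 3 × 64 = 237, V = 3 × 25 + 3 × 16 + 2 × 9 = 141.
- Poisson variance at the mean rate: 1.125, so s = 1.125/50 = 0.0225 and τ² = 1.125 × 0.01/0.99 = 0.01136.
- Numerator: 8 × 0.0225 × (0.0225 + 6 × 0.01136) = 0.01632.
- Denominator: 27 × 0.0225 + 123 × 0.01136 = 2.005.
- Var = 0.00814, SE = 0.0902, power = Φ(0.25/0.0902 − 1.96) = 0.79.

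The protocol states 0.80. The other three rows give 0.908, 0.967 and 0.990 against 0.91, 0.97 and 0.99. The calculation contains no covariates, so it neither supports nor refutes the concern.

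**2. What the timing of the visit covariate does to a treatment outcome.** The protocol gives no visit rates, so every rate here is an assumption.

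*Simple comparison.* Youth with gamma frailty, control event rate 0.3, true ratio 1.25, adjuster log(1 + total visits in the same period), where total = outcome visits + other visits:

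| Other visits per youth | No visit adjuster | Same-period visits |
|---|---|---|
| 0.5 | 1.24 | 1.13 |
| 1 | 1.25 | 1.18 |
| 2 | 1.24 | 1.20 |

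On the log scale, 1.13 loses 1 − ln 1.13/ln 1.25 = 1 − 0.122/0.223 = 45% of the effect, and 1.20 loses 1 − 0.182/0.223 = 18%.

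*On the protocol's design matrix.* Cluster and period effects, 200 youth per cluster-period, 60 replicates, about 2.5 visits generated per outcome event, true ratio 1.25:

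| Control rate | Other visits | None | Pre-arrest visits | Same-period, linear | Same-period, log(1+x) |
|---|---|---|---|---|---|
| 1.0 | 0.5 | 1.258 | 1.255 | 1.032 | 1.011 |
| 1.0 | 2 | 1.264 | 1.259 | 1.088 | 1.069 |
| 1.0 | 6 | 1.260 | 1.260 | 1.167 | 1.155 |
| 0.3 | 0.5 | 1.241 | 1.242 | 1.104 | 1.055 |
| 0.3 | 2 | 1.227 | 1.225 | 1.130 | 1.121 |
| 0.3 | 6 | 1.250 | 1.244 | 1.200 | 1.205 |

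Pre-arrest visits cause no attenuation. Same-period visits give about 1.01 to 1.20.

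**3. What an attenuated ratio would mean for power.** Using the formula in step 1 and treating the attenuated value as the ratio under test:

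| Ratio | Power, m = 50 | Power, m = 66 |
|---|---|---|
| 1.25 | 0.79 | 0.89 |
| 1.20 | 0.61 | 0.73 |
| 1.13 | 0.32 | 0.39 |

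These are nominal values: adjustment would also change the standard error, which is ignored here.

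**4. Direction for opioid events.** True ratio 0.80, control rate 0.05 to 0.3, 1 to 2 other visits per youth, same log(1 + total visits) adjuster (all assumed):

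- LHS leaves other visits unchanged: about 0.80 to 0.84.
- LHS raises other visits by 25%: about 0.63 to 0.69.
- LHS raises other visits by 50%: about 0.51 to 0.58.

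In the last two cases the ratio moves away from 1 and overstates the benefit, because an LHS youth is compared with a control youth who reached the same visit total with less treatment and more harm.

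**The case against.** The strongest reply is that the protocol never says the covariate visits are concurrent. It collects five pre-study years of data and Medicaid claims over all ten years, so prior utilisation is an equally available reading, and under it there is no bias. A look-back window is also ordinary SAP content, and the SAP is not shown. The first part stands: bias cannot be asserted as fact. The second part does not dispose of the point. The protocol does more than omit a detail: it names a class of covariate that overlaps its own primary outcomes, and an SAP that followed the sentence literally would inherit the problem.

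Four stronger readings are tempting, and the documents do not support them.

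- *The effect is adjusted away.* The visit window is unstated, so the plan permits this but does not require it.
- *The bias is always toward 1.* Step 4 shows it can exaggerate benefit for opioid events.
- *The survey and SIC variables dilute the Aim 4 effect.* They enter in a later step with a stated predictive purpose, and would alter only an LHS estimate read from that step. The protocol does not say which step supplies the reported effect.
- *The Aim 3 staff covariates distort the main rate ratio.* They belong to a linear mixed model for staff scale scores, which yields no rate ratio. Only the implementation and fidelity measures are described as time-varying, and only in Aim 4.

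On placement, it remains an inference that it would be a regression covariate. The planned log-days offset does not settle this, because it is defined by days of exposure to the implementation.

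**Conclusion.** The concern holds as a defect in what the plan allows. The effect model names health visit data as a predictor with no pre-arrest limit, while the same records define initiation, engagement and the opioid outcomes. Control for commitments and residential placement adds a second adjuster that can be measured after LHS starts. If the text is followed with same-period data, the rate ratio is pulled toward 1 for initiation and engagement. For opioid events it may be pushed away from 1 if LHS raises other visits.

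The sizes rest on assumed event and visit rates, frailty and covariate form, and on a covariate built to contain the outcome. They show the consequence of one reading and do not estimate this trial's bias. What does not depend on the chosen rates is the contrast: visits before the index arrest leave the ratio unbiased in these simulations, and visits that include outcome events do not. This should be corrected before analysis.

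**What to change.** 1. In Aim 4 Analyses, restrict youth-level covariates in the LHS effect model to values fixed before the index arrest: demographics, prior arrests, and health visits in a set look-back such as 12 months. For youth with several arrests, define the index arrest so that the look-back does not reach into follow-up from an earlier arrest under LHS.
2. Account for placement through days in the community in the offset, not as a covariate, and reword the offset definition to match. The result is then a rate per day in the community.
3. State that the reported LHS effect comes from this model, and label the later survey and SIC step as explanatory.
4. As a separate and secondary point, in Aim 3 Step 1 use first-survey values of job satisfaction, turnover intentions and burnout.

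The cost is a change of wording and slightly less covariate information. The pre-arrest records are already within the planned 10-year extract.
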